## Abstract

**Introduction:**

Respiratory tract infections (RTIs) in children are common and present major resource implications for primary care. Unnecessary use of antibiotics is associated with the development and proliferation of antimicrobial resistance. In 2016, the National Institute for Health Research (NIHR)-funded ‘TARGET’ programme developed a prognostic algorithm to identify children with acute cough and RTI at very low risk of 30-day hospitalisation and unlikely to need antibiotics. The intervention includes: (1) explicit elicitation of parental concerns, (2) the results of the prognostic algorithm accompanied by prescribing guidance and (3) provision of a printout for carers including safety netting advice. The CHIldren’s COugh feasibility study suggested differential recruitment of healthier patients in control practices. This phase III ‘efficiently designed’ trial uses routinely collected data at the practice level, thus avoiding individual patient consent. The aim is to assess whether embedding a multifaceted intervention into general practitioner (GP) practice Information Technology (IT) systems will result in reductions of antibiotic prescribing without impacting on hospital attendance for RTI.

**Methods and analysis:**

The coprimary outcomes are (1) practice rate of dispensed amoxicillin and macrolide antibiotics, (2) hospital admission rate for RTI using routinely collected data by Clinical Commissioning Groups (CCGs). Data will be collected for children aged 0–9 years registered at 310 practices (155 intervention, 155 usual care) over a 12-month period. Recruitment and randomisation of practices (using the Egton Medical Information Systems web data management system) is conducted via each CCG stratified for children registered and baseline dispensing rates of each practice. Secondary outcomes will explore intervention effect modifiers. Qualitative interviews will explore intervention usage. The economic evaluation will be limited to a between-arm comparison in a cost–consequence analysis.

**Ethics and dissemination:**

Research ethics approval was given by London-Camden and Kings Cross Research Ethics Committee (ref:18/LO/0345). This manuscript refers to protocol V.4.0. Results will be disseminated through peer-reviewed journals and international conferences.

**Trial registration number:**

ISRCTN11405239.

Strengths and limitations of this studyInformed by a feasibility study this ‘efficient-design’ cluster randomised controlled trial uses routinely collected aggregated measures for the coprimary outcomes, and avoids postrandomisation recruitment bias associated with individual patient consent.The study will recruit practices across England, thus including research-naïve practices and those serving diverse socioeconomic populations.The complex intervention, embedded within practice electronic health records, stems from a 5-year NIHR-funded programme and includes: (1) a prognostic algorithm to stratify children’s risk of hospitalisation due to respiratory infection in the following 30 days; (2) tools to improve patient-doctor communication; and (3) home care information (an alternate treatment action for clinicians).The design only allows for dispensing to be related to the number of children registered at the practice rather than the number consulting for respiratory tract infections (RTI), and it will not allow quantification of delayed prescribing.The other primary outcome is hospitalisation for RTI, and this relies on the quality of the data collected by Clinical Commissioning Groups—any difficulties obtaining this information or limitations of this efficient design will be reported.

## Introduction

### Background

Acute respiratory tract infections (RTI) in children are a common reason for antibiotic prescribing. In English primary care, most antibiotics are prescribed for conditions that only sometimes require antibiotic treatment, depending on patient-specific indicators.^1^ Although there has been a decline in prescribing for uncomplicated RTI in England over the last decade, more than a third of children were still prescribed antibiotics for these infections.^2^ Clinical uncertainty in primary care regarding the prognosis of children with RTIs (ie, knowing which children will and won’t subsequently deteriorate) contributes to the unnecessary use of existing antibiotics, which is associated with increasing antimicrobial resistance.^3 4^ Qualitative work from our 5-year National Institute for Health Research (NIHR)-funded ‘TARGET’ programme grant, completed in 2016, identified this uncertainty as a major driver of antibiotic prescribing.^5^ We hypothesised that improved identification of children at very low risk of future hospitalisation might help reduce clinical uncertainty.^6^ As part of the ‘TARGET’ programme, we developed a prognostic algorithm that could be used by clinicians to identify children at very low risk of hospitalisation as well as tools to improve patient-–doctor communication.^7^

### Lessons learnt from the feasibility cluster randomised controlled trial

Findings from across the ‘TARGET’ programme were used to develop a complex intervention designed to reduce antibiotic prescribing. The subsequent feasibility cluster randomised controlled trial (RCT) for CHIldren’s COugh (CHICO) showed significant prescribing reductions in both arms of the trial compared with the cohort data of the programme but also exposed both lower prescribing levels and differential recruitment of healthier children in the control arm.^8^ In the qualitative interviews, clinicians reported preferential recruitment of less unwell children as these were quicker to manage and therefore easier to recruit. To negate differential recruitment, and conserve resources, an ‘efficient design’ was proposed for the full trial. Efficient design trials often use routinely collected data.^9^ In the case of CHICO using aggregated data, this both avoids the need for individual patient consent (and differential recruitment) and utilises existing practice level data. This simpler design, placing fewer demands on clinicians and practices compared with other studies, will also encourage the recruitment of research-naïve practices. The primary outcomes are routinely collected antibiotic dispensing data, collected by ePACT2 for the National Health Service (NHS) prescribing services,^10^ and hospital admission data collected by all English Clinical Commissioning Groups (CCGs decide what services are needed for diverse local populations, and ensure that they are provided (https://www.england.nhs.uk/ccgs/). They also hold responsibility for local antimicrobial prescribing guidelines. Lessons learnt from the feasibility study also suggested better use of the tool would be facilitated if the intervention was embedded within the practice electronic health record system. The intervention in this study has thus been embedded in the Egton Medical Information Systems (EMIS) electronic patient record system, used in 56% of the primary care practices in England.^11^

### Aims and objectives

The aim of the CHICO RCT is to reduce antibiotic prescribing among children presenting with acute cough and RTI without increasing hospital admission for this condition.

The objectives are to determine whether the CHICO intervention decrease the number of dispensed prescriptions for oral amoxicillin and macrolide antibiotics (the predominant antibiotics given to children presenting with acute cough and RTIs in the UK) for children aged 0–9 years (efficacy comparison) and to determine if the CHICO intervention does not increase hospital admissions for children with a hospital diagnosis of RTI (non-inferiority comparison).

## Methods and analysis

### Study design

The CHICO RCT is an efficient, pragmatic open-label, two-arm (intervention vs usual care) trial with an embedded qualitative study, aimed at reducing antibiotic prescribing among children presenting with acute cough and RTI, with randomisation at the practice level, using routine antibiotic dispensing and hospitalisation data to assess effectiveness.

### Study population, setting and recruitment plan

The study population is children aged 0–9 years presenting with acute cough and RTI. Oral suspensions are more often given to this age group. The setting is consultations in primary care practices with prescribing clinicians in diverse regions across England. Recruitment is at the practice level, so consent is not required for individual participants. Recruitment of practices is via CCGs and by using the Clinical Research Network (CRN) who support patients, the public and health and care organisations across England to participate in high-quality research (https://www.nihr.ac.uk/explore-nihr/support/clinical-research-network.htm). All CCGs are already committed to national AMR strategies and an initial approach to several CCGs about collaboration in this study has been enthusiastically welcomed. CCGs with 15 or more EMIS practices will be targeted and we will use a member of the CCG medicines management team as the primary contact given the established links they already have helping to provide routine data.

### Eligibility

#### Inclusion

GP practices in England using the EMIS electronic patient record system where the local CCG has agreed to provide data and the practice consented to take part.

#### Exclusion

Practices will be asked directly whether they are participating in any antimicrobial stewardship activities during our study period and these will be recorded. If these activities involve concurrent intervention studies where there is potential to confound or modify the effects of the intervention these practices will be excluded. Practices involved in the CHICO feasibility study or are merging or planning to merge with another practice will also be excluded.

### Treatment arms

#### Intervention

The theory-informed intervention^12^ consists of both a clinician-focused algorithm to predict risk of hospitalisation for RTI in the following 30 days, in children with acute cough and RTI, and carer-focused personalised information recording decisions made at the consultation and safety netting information.^13^

The algorithm contains seven predictors (mnemonic STARWAVe): Short illness duration (parent/carer reported ≤3 days); raised Temperature (parent/carer reported severe in previous 24 hours or ≥37.8°C on examination); age of child (<2 years); intercostal or subcostal Recession on examination; Wheeze during chest stethoscope examination; history of Asthma and Vomiting (parent/carer reported moderate or severe in the 24 hours prior to consultation). The actions related to the algorithm scores are shown in table 1, in each case the algorithm result (eg, low-risk group) automatically appears and the pop-up text is available if the clinician hovers over the result. The algorithm is intended as a supportive additional component of a consultation in which it is likely that a number of aspects will inform the clinical decision making, including whether or not to prescribe antibiotics.

**Table 1 T1:** Text for algorithm result

Algorithm result	Pop-up text
Very low-risk group	Very reassuring CHICO score: 0 or 1 CHICO predictors:>99.6% of children will recover from this illness with home care. Consider a no or delayed antibiotic prescribing strategy. CHICO leaflet and letter covers common concerns and safety netting advice.
Average risk group	Reassuring CHICO score: 2 or 3 CHICO predictors:>98% of children will recover from this illness with home care. Consider no or delayed antibiotic prescribing strategy. CHICO leaflet and letter covers common concerns and safety netting advice.
Elevated risk group	Safety netting needed: 4+CHICO predictors: This is more than average, but >87% of children will still recover from this illness with home care. Highlight SAFETY NETTING advice in CHICO leaflet.

CHICO, CHIldren’s COugh.

We will enrol a champion (eg, a GP, nurse or practice manager) at each practice to help encourage and monitor the use of the intervention. These champions will help to set up the intervention and run monthly queries of intervention use via EMIS that will be monitored centrally by the study team.

#### Training for practitioners in the intervention arm

The intervention clinicians will be provided with print and on-line evidence-based information to describe why, how and when to use the intervention. A practice champion will distribute the self-directed training materials within the practice and encourage all clinicians to use the intervention appropriately. In the training package for clinicians, it will be emphasised that the primary purpose of the intervention is to support the care of the larger proportion of children (69%) who have a very low risk of hospitalisation.

#### Usual care

The clinicians in practices randomised to the comparator arm will be asked to treat children presenting with acute cough and RTI as they would normally. Baseline and follow-up data on control practices will be collected but no data are being collected directly from the clinicians, no practice champions identified or specific contact being made.

### Patient and public involvement

This intervention has been developed collaboratively with our parent advisory group (PAG) and clinical advisory group throughout the ‘TARGET’ programme. Their comments and suggestions about the format of the intervention and parent/carer materials have informed both the intervention and the design of the earlier feasibility study.

Similar involvement will be sought for the trial. We will seek agreement from a newly formed PAG to meet throughout the study to report on progress of the study and discuss issues that arise during the study. PAG members will input into all the materials for parents/carers as they are further developed including any patient-facing tools. We will also form a clinician and pharmacist advisory group to assist with the implementation and any further refinements to the intervention. They will meet once in person and then contribute by Skype or email to refine GP information and intervention delivery.

### Data collection and randomisation

Data collection takes place when both the individual practice and allied CCG agree to participate. Data will be entered onto a purpose designed database, validation and cleaning will be carried out throughout the trial. Only the administrative team and analysts will be able to access this data.

The number of dispensed amoxicillin and macrolides antibiotics given to children aged 0–9 years will be taken from the routine data source, epact2,^10^ which provides practice-specific information by each 5-year age epoch. Data will be collected from CCGs for every participating practice with regards to the number of hospitalisations and emergency department attendances for RTIs. Only fully anonymised data sets will be sent from the GP practices and CCGs. This will be sent to a secure NHS e-mail address. We will collect data for the 12-month period each practice will be in the study and the 12-month period prior to randomisation. An ‘implementation period’ of around 1 month will allow time for the practices to instal the intervention and encourage staff to use it. Any data collected during this period will not be used in the analysis. Where data are suppressed, owing to a low number of events, practices will be asked to provide aggregate 12-month data for baseline and follow-up. Practice list size data, per month and 5-year epoch, will be obtained from the NHS digital website. In the unlikely event that a practice no longer wishes to participate, we will request all outstanding data collected up until the point of withdrawal. For intervention practices only, monthly intervention usage data will be captured. The data will be extracted from the EMIS system and will include how often the intervention is being used and by whom. Fidelity will be measured from the analysis of intervention data usage, scrutiny of the follow-up questionnaires and qualitative interviews.

The trial is supported by the Bristol Randomised Trials Collaboration (BRTC). The trial will conform to the BRTC standard operating procedures. The BRTC central research team will help prepare the trial documentation and data collection forms, specify the randomisation scheme, develop and maintain the study database, check data quality, monitor recruitment and carry out analyses in collaboration with the investigators. Both an independent trials steering committee (TSC) and data monitoring committee (DMC) will be appointed.

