### Internal pilot study

An internal pilot phase lasting 3 months and using 4 or more CCGs to recruit 60 practices will help establish how many CCGs we will eventually need to approach. Stop-go (traffic light) criteria will be used for (1) practice recruitment, (2) identification of a practice champion, (3) intervention use and (4) ability to obtain dispensing data from the CCGs. A green light will be given for 80+% success (90% for dispensing data) and an amber light to implement remedial action at 70%–79% (80%–89% for dispensing data). A red light would indicate either a further pilot is needed or stopping the trial.

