### Sample size determination

Both sample size calculations assume 90% power and a conservative two-sided alpha of 0.025 to take account of the two coprimary outcomes. Both sample sizes also assume an intracluster correlation coefficient of 0.03 (which has been described as the upper CI for ICCs in efficient cluster randomised trials,^14 15^ an estimated coefficient of variation of 0.65 (to take account of differences in cluster size^16^ and an assumption of 750 children on average aged 0–9 years registered per practice (based on Bristol & Bath CCG data). Expected differences assumed: (1) a reduction in dispensing rate from 33 prescriptions per 100 registered children aged 0–9 years to 29 (or fewer) prescriptions (ie, ≥10% overall reduction); and (2) a hospitalisation rate that is no more than 2% in the intervention arm, compared with the control arm which is estimated to be 1%. This is based on a non-inferiority margin of 1%, however, the investigators wanted to err on the side of caution and use a two-sided alpha for the sample size calculation. This gave an overall sample size requirement of 310 practices; 155 intervention and 155 control practices.

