### Data analysis

#### Quantitative data analysis

All analyses and reporting will be in line with Consolidated Standards of Reporting Trials (CONSORT) guidelines and its extension for cluster randomised trials.^20^ Primary analyses will be conducted on an intention-to-treat basis, a per-protocol analysis will also be conducted as part of the sensitivity analyses. A full CHICO statistical analysis plan will be developed and agreed by the TSC prior to undertaking analyses of the main trial. The statistical analysis plan will include health economics and qualitative analysis subsections. At the end of the trial, all outcomes will be described and compared with the appropriate descriptive statistics where relevant: mean and SD for continuous and count outcomes, medians and IQR if required for skewed data and numbers and percentages for dichotomous and categorical outcomes. Depending on the dispersion of the data we may use linear regression or a random effects Poisson regression (negative binomial regression) model to analyse both coprimaries, with CCG included as a random effect. This has the advantage of incorporating person-years follow-up (number of children at a practice multiplied by the length of follow-up for that practice) and examining clustering by CCG. Each coprimary will be adjusted for baseline dispensing rates or hospitalisation rates, using the 12 months of data collected prior to randomisation. Effects of number of practices within CCGs and number of patients within each practice will also be investigated in a sensitivity analysis. Other baseline characteristics between practices will be examined to ensure randomisation is balanced in the two arms. Any differences in excess of 0.5 SDs or 10% or more will be controlled for in sensitivity analyses to ensure that the imbalance does not affect the overall result. The effects of missing data will be explored using sensitivity analyses. We anticipate no more than 10% missing data and that it will be missing at random. The pattern and extent of missing data will be explored and any changes to the methods described in the analysis plan will be fully justified in the study report and publication. All quantitative data will be analysed using Stata version 15.

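### Admission totals that stay suppressed are missing because they are low, so the expectation of at most 10% missing at random does not fit this co-primary

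*Protocol article*

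**What the plan says.** Under Data collection and randomisation, hospital admissions for each practice come from the CCG and dispensing comes from ePACT2. The same section adds: "Where data are suppressed, owing to a low number of events, practices will be asked to provide aggregate 12-month data for baseline and follow-up". It names neither the series affected nor the cut-off.

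Table 2 defines both co-primaries as 12-month practice rates, so an annual total is the figure the analysis needs. Quantitative data analysis then states, for all data: "We anticipate no more than 10% missing data and that it will be missing at random". It also promises sensitivity analyses for missing data and a look at its pattern and extent.

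Two other sections bear on recovery. Usual care says control practices have no champion and no specific contact. Blinding says practices know their allocation.

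**The concern.** A count withheld because it is small is missing because of its own value. That is the opposite of missing at random, and the plan describes the mechanism itself. The affected outcome is the safety co-primary, on which the claim of no excess admissions rests.

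The fallback has a second weakness. It asks the practice, which knows its arm, and not the CCG that supplies the other counts. Low-count practices would therefore be measured through a different source. Intervention practices have a champion in regular touch with the study team and control practices do not, so the response could differ by arm. If fewer low totals come back from control practices, the control rate looks too high and the intervention looks safer than it is.

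**Working it through.** **Inputs from Sample size determination.** "Both sample size calculations assume 90% power and a conservative two-sided alpha of 0.025", which leaves 0.0125 in the non-inferiority tail; "an intracluster correlation coefficient of 0.03"; "an estimated coefficient of variation of 0.65"; "an assumption of 750 children on average aged 0–9 years registered per practice"; admissions of 1% against 2%, with a margin of 1% read as absolute; 155 practices per arm.

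**The plan's own figure.** Design effect = 1 + ((1 + 0.65²) × 750 − 1) × 0.03 = 32.98. At 155 practices per arm the effective size is 155 × 750 / 32.98 = 3,525, which gives power of 0.918 for dispensing and 0.888 for admissions (1% v 2%). An arcsine calculation for admissions gives 157 per arm, 314 in all, against the stated 310. The inputs are therefore read as the plan meant them.

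**Which series is exposed.**
- Admissions: 750 × 0.01 = 7.5 a year; 7.5 / 12 = 0.625 a month.
- Dispensing: 750 × 0.33 = 247.5 a year, about 21 a month.
- For a Poisson mean of 0.625, P(0) = 0.535, P(1–4) = 0.464 and P(5 or more) = 0.0005. With an assumed cut-off of 5, almost no month would be reported with a usable non-zero count. If the data arrive monthly, the request for annual totals carries the whole outcome.

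**How many annual totals could be hidden.** Assumptions: gamma list sizes (mean 750, CV 0.65), gamma practice rates with CV from 0.3 to 1.72, Poisson counts, and every 12-month count below 5 hidden, zeros included. The upper CV is what the plan's ICC implies at a 1% rate: √(0.03 × 0.99 / 0.01) = 1.72. The share hidden is 0.378 to 0.664 at 1% and 0.150 to 0.550 at 2%. To keep missingness at or below 10% at a 1% rate, recovery must reach 1 − 0.10/0.378 = 73.5% at CV 0.3 and 1 − 0.10/0.664 = 84.9% at CV 1.72.

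**Effect on the comparison.** The simulation used 155 practices per arm, a ratio of totals with cluster-robust errors, and true rates of 2% and 1%. Unrecovered practices were left out. Each cell gives the estimated difference in percentage points (truth 1.00) and the probability of wrongly concluding non-inferiority.

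| Practice-rate CV | All recovered | 75% in both arms | None recovered | 100% intervention, 75% control |
|---|---|---|---|---|
| 0.3 | 1.000; 0.014 | 0.992; 0.021 | 0.949; 0.056 | 0.978; 0.029 |
| 0.5 | 0.998; 0.019 | 0.992; 0.016 | 0.937; 0.048 | 0.962; 0.040 |
| 1.0 | 1.003; 0.019 | 1.027; 0.020 | 1.046; 0.012 | 0.915; 0.053 |
| 1.72 | 0.993; 0.030 | 1.107; 0.016 | 1.474; 0.002 | 0.839; 0.068 |

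Only the last column favours non-inferiority in every row. Its overall missingness is (0 + 0.095)/2 = 4.8% at CV 0.3 and (0 + 0.166)/2 = 8.3% at CV 1.72, so meeting the 10% expectation gives no protection. If zeros are reported and only low non-zero totals are hidden, the same pattern of recovery gives differences of 0.94 to 0.98.

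**The case against.** A reader might infer that the plan biases the non-inferiority test toward success. The documents do not support that. The sentence that admits suppression also supplies the remedy, and the remedy delivers the 12-month figure that Table 2 requires. A hidden month is not a missing outcome once the annual total is in hand. Nowhere does the article say that suppressed practices are dropped. With full recovery there is no bias. With equal recovery of 75% or 90%, false non-inferiority is 0.016 to 0.023, against 0.014 to 0.030 with everything recovered. With no recovery, the difference shrinks at low between-practice variation and grows at high variation. At the variation implied by the plan's ICC, power under equal rates falls from 0.96 to 0.50, which works against success. That ICC is described as an upper limit, so 1.72 is a high value, but the direction is not settled. All of this stands.

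It is also fair that the 10% wording is an expectation and not an analysis rule, that sensitivity analyses are promised, and that an unseen analysis plan may say more. Poorer response from control practices is a possibility the article does not predict, since all practices complete questionnaires at baseline and 12 months. This limits the point but does not remove it: the stated expectation still conflicts with the mechanism that the article describes.

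A reader might also want the pilot criterion, "ability to obtain dispensing data from the CCGs", extended to completeness of hospital data. A 3-month pilot cannot test that on practices that have finished 12 months of follow-up, and the article already discloses its reliance on CCG hospital data. That extension is not part of this point.

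**Conclusion.** The point holds in a limited form. For suppressed admission totals that are not recovered, missing at random is wrong by construction, and the 10% ceiling depends on recovering roughly three quarters or more of them. If recovery is lower in control practices, the comparison shifts modestly toward non-inferiority: a true 1.00-point excess appears as 0.84 to 0.98 points. With equal recovery the shift in the test is small. With no recovery its direction depends on between-practice variation.

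These sizes rest on an assumed cut-off of 5, on annual as well as monthly suppression, on zeros being hidden, on an absolute margin, and on 75% as an illustrative recovery. The simulation omits the baseline adjustment and CCG random effect that the plan intends. That admissions are the suppressed series is an inference from the planned rates. The matter should be corrected, but it does not undermine the design.

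**What to change.** 1. Request 12-month baseline and follow-up admission totals, not only monthly counts, from the CCG for every practice in both arms.
2. Approach the practice only where the CCG total is still suppressed, with the same request and the same reminders in both arms.
3. State the suppression cut-off and whether zeros are hidden.
4. Keep practices with unrecovered totals in the analysis, with the count bounded between the lowest and highest suppressible values. This can be an interval-censored count model or a best-case and worst-case sensitivity analysis.
5. Report recovery by arm.
6. Remove the missing-at-random expectation for suppressed admission counts.

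The cost is a slightly longer data request and one extra sensitivity analysis. The bounded analysis is the simpler choice if an interval-censored likelihood with a CCG random effect proves awkward to fit.
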